**2. Statistical methods**

**Statistical description**

1) Whether it is in accordance with normal distribution; if not, modify the statistical method or transfer the data;

2) Whether there is outlier: With statistical and special analysis to determine to use or not

3) Whether there is any missing value: when one of the main curative effect indexes is not found in individual subjects, switch of the last observation data is made.

4) The proportion of off patients: should not be greater than 20%, otherwise should be analyzed;

5) Descriptive statistics analysis: point out the mean, standard deviation, maximum, minimum, credibility interval, credibility rate, etc.

**3. Analysis method**

1) Measurement data: t test, paired t test, rank-sum test, paired rank-sum test and other methods;

2) Enumeration data: Fisher’s exact test, etc.; rank-sum test is adopted for ranked data.

3) Curative effect analysis: CMH chi-square test or logistic regression is used for enumeration data; variance analysis or rank-sum test is adopted for measurement data according to the characteristics of data; Kaplan-meier method or Cos regression is adopted for survival data.

4) FAS analysis and PP analysis: the two analyses are performed at the same time for the main curative effect indexes.

**4. Statistical expression**

Bilateral inspection is adopted generally, P less than or equal to 0.05 will be considered a statistically significant discrimination.

**5. Statistical software**

SPSS software is used for analysis.

**6. Test type**

Superiority test

**7. Content of statistical analysis**

1) Distribution of the two groups of cases: total off rate and the off rate due to adverse events in the two groups are compared with chi-square test.

2) Comparable analysis: demographic data and other basic indexes are compared to measure the comparability of the two groups.

3) Compliance analysis: to compare the two groups of patients that whether they are on a stricter medication regime, or use drugs and food forbidden in the regime.

4) Validity analysis: the main index and overall index are analyzed with PP and FAS analysis; because this study is a multicenter clinical trial, during the analysis, the influences of center effect on the curative index should be considered.

5) Security analysis: first, according to the requirements of adverse reaction correlation, adverse events and adverse reactions of the two groups should be listed, including the number of adverse events, cases of laboratory examination indexes turned from normal to abnormal before and after the test and different rate). The chi-square test is adopted to analyze adverse reactions.

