**Date final：2011/02/01**

**version：1.0**

**Protocol summary**

| Ttitle | Phase II study of *Pseudomonas aeruginosa*-mannose-sensitive hemagglutinin(PA-MSHA) in combination with capecitabine for Her-2–negative metastatic breast cancer |
| --- | --- |
| Study site | Fudan university cancer centre |
| Study objectives | To assess the efficacy and safety of PA-MSHA in combination with capecitabine in Her-2 negative metastatic breast cancer. |
| Study design | Phase II, single arm, single center clinical trial. |
| Study population | MBC pretreated with antracycline and taxane. |
| Number of patients | 96 |
| Study regime | PA-MSHA 1 mg was administered subcutaneously every other day and capecitabine1000 mg/m2 orally twice a day for 2 weeks on, 1 week off. |
| Primary endpoint | Progression free survival（PFS） |
| Secondary endpoint | Overall response rate（ORR）、Overall survival（OS）、safety、exploratory endpoints such as immune index. |
| Inclusion criteria | 1) Women aged between 18 and 70 years；  2) Histologically confirmed Her-2–negative MBC；  3) Not suitable for local treatment;  4) Pretreated with antracyclene and taxane；   1. Prior capecitabine-containing therapy was permitted if the disease had responded to the drug previously and progressed at least 4 months after drug discontinuation； 2. ECOG performance status of no more than 2；   7) Adequate organ function；  8) Having the following laboratory values; WBC≥4×109/L；Hb≥90 g/L；plt≥100×109/L；  9) Written informed consent should be obtained before study procedure. |

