**II.Study design**

This phase II, single centre, single arm, open-label study is designed to evaluate the efficacy and safety of capecitabine plus PA-MSHA in subjects with Her-2 negative metastatic breast cancer pretreated with anthracycline and taxane.

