**2. Reporting period of adverse events**

Adverse events occurring between randomization and the last follow-up, no matter related to the research drug or not, should be filled in the case report form. In addition, any adverse incident happens after the reporting period, if being estimated associated with the research drug, the researcher also should report it as adverse events.

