**XII. Sample size**

It is expected that the PFS will be prolonged from 4.2 months with monotherapy of Xeloda to 5.7 months after combined with pseudomonas aeruginosa injection. So according to a=0.05 and power of 85%, the needed sample size is 88 cases; 96 patients were required in consideration of 10 % expulsion rate.

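### Section XIV.7 prescribes two-group, multicentre analyses for a single-arm, single-centre trial, and section XIV never ties the primary PFS analysis to the 4.2-month benchmark behind the sample size

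*Protocol*

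**What the plan says.** **Design.** The Protocol summary gives "Phase II, single arm, single center clinical trial". Section II agrees: "This phase II, single centre, single arm, open-label study is designed to evaluate the efficacy and safety".

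**Sample size (section XII).** "It is expected that the PFS will be prolonged from 4.2 months with monotherapy of Xeloda to 5.7 months" once PA-MSHA is added. With alpha 0.05 and 85% power this gives 88 cases, raised to 96 for dropout. Section I.2 shows where 4.2 months comes from: it is the median PFS of the capecitabine-alone arm of a cited phase III trial.

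**Analysis (section XIV).**
- XIV.3: "Kaplan-meier method or Cos regression is adopted for survival data".
- XIV.4: testing is generally two-sided, with significance at 0.05.
- XIV.6, in full: "Superiority test".
- XIV.7 item 1: "total off rate and the off rate due to adverse events in the two groups are compared with chi-square test". Items 2, 3 and 5 likewise refer to two groups, for baseline data, compliance and adverse events.
- XIV.7 item 4: "because this study is a multicenter clinical trial, during the analysis, the influences of center effect on the curative index should be considered".

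**Elsewhere.** Section XI.2 opens its reporting window with "Adverse events occurring between randomization and the last follow-up". Sections XIII.2 and XV speak of test centres in the plural.

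**The concern.** XIV.7 reads as text carried over from a randomised multicentre trial. A statistician following it would look for a second group and for several centres, and find neither.

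The comparison that the design does need is not stated. The trial was sized to show that PFS exceeds 4.2 months, but section XIV mentions neither that figure, nor a historical control, nor a one-sample test, nor a rule for success. The study is open-label with investigator-assessed response, and the opening of section XIV lets the SAP change during the trial as long as it is finished before data lock. The form and sidedness of the primary test could therefore be settled after outcomes are visible. A result reported only as superiority could also be taken for a concurrent comparison, which one arm cannot give.

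**Working it through.** **1. What section XII's 88 corresponds to.** Inputs from sections XII and XIV.4: 4.2 and 5.7 months, alpha 0.05 (two-sided: z = 1.960), power 85% (z = 1.036). Assumptions: both figures are medians (section XII says only PFS; section I.2 gives 4.2 as a median) and PFS is exponential. The hazard ratio is then 4.2/5.7 = 0.737, with ln(0.737) = −0.305.

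- One-sample, median scale, two-sided: (1.960 × 4.2 + 1.036 × 5.7)² / (5.7 − 4.2)² = 88.9.
- One-sample log-rank, two-sided: expected events under the null = (1.960 + 1.036 × √0.737)² / (1 − 0.737)² = 117.3; observed events = 117.3 × 0.737 = 86.4.
- One-sample, log-hazard scale, one-sided: (1.645 + 1.036)² / 0.305² = 77.1 events. If the 24-month study period were split into 12 months of accrual and 12 of follow-up (an assumption), 87.8% would have an event, giving 77.1/0.878 = 87.8 patients.

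Other one-sample choices move the figure, for example 96.3 events on the log-hazard scale two-sided. Section XII gives no formula, so which variant was used is unknown. The stated 88 lies within the one-sample range.

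**2. The same inputs as a two-group trial (1:1).**

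- Schoenfeld, two-sided: 4 × (1.960 + 1.036)² / 0.305² = 4 × 96.3, i.e. 386 events. One-sided: 4 × 77.1, i.e. 309.
- Freedman, two-sided: (1.737/0.263)² × (1.960 + 1.036)², i.e. 392 events.
- Two-sided power with 88 events in total: Φ(√(88/4) × 0.305 − 1.960) = Φ(−0.53), about 30%.

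The smallest two-group figure is 309/88 = 3.5 times the stated one. Section XII therefore describes a one-sample comparison with 4.2 months.

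**3. Section XIV set against that comparison.**

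| Place | Content | In one arm at one centre |
| --- | --- | --- |
| XIV.3 | Kaplan-Meier | Usable as an estimate; not linked to 4.2 months |
| XIV.3 | Cox regression | No treatment contrast |
| XIV.6 | Superiority | Coherent against a fixed value; none is named |
| XIV.7 item 1 | Two-group test of withdrawals | Cannot be run; reduces to rates |
| XIV.7 item 2 | Baseline comparability | No meaning |
| XIV.7 item 3 | Two-group compliance | Cannot be run; reduces to rates |
| XIV.7 item 4 | FAS and PP; centre effect | First part stands; second cannot be run |
| XIV.7 item 5 | Adverse-event listing and laboratory shifts; chi-square test | Listing and shifts stand; a between-group test cannot be run |

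**The case against.** The strongest reply is that the pieces of a valid test are already in the Protocol. Section XII fixes 4.2 months and alpha, XIV.4 fixes two-sided testing, and XIV.3 names Kaplan-Meier. A 95% interval for the Kaplan-Meier median that excludes 4.2 is a test by inversion. Naming the exact test is commonly left to a SAP, and section XIV requires one. Much of this stands, so the PFS limb is weaker than the design contradiction. What remains is that no sentence joins the pieces, and XIV.7, which sets out the content of the analysis, describes a different trial.

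Four stronger readings are tempting, and the Protocol does not support them.

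- *All of section XIV is unusable.* It is not. The two-group and multicentre wording is confined to XIV.7. The analysis sets, descriptive rules, significance level and software work with one arm, and the paired tests in XIV.3 suit before-and-after data.
- *The superiority label shows that two groups were meant.* PFS above a fixed 4.2 months is itself a superiority hypothesis. XIV.6 lacks only its comparator.
- *The benchmark could be picked after the data are seen.* Section XII sets it in advance. Only the form and sidedness of the test are open.
- *The defect can be sized by the chance of a false success.* Section I.2 reports phase II capecitabine-alone medians of 3.1 to 4.9 months. If the true value here were 4.9 with PA-MSHA adding nothing, the shift would be √88 × ln(4.9/4.2) = 1.446. A test against 4.2 would then succeed about 30% of the time (two-sided 5%) or 42% (one-sided 5%). The arithmetic is right for 88 events and exponential PFS, but it measures uncertainty in a historical benchmark. The test proposed below shares that uncertainty.

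**Conclusion.** The point holds in two parts. First, XIV.7 contradicts the Protocol summary and section II. Every one of its five items contains a two-group or centre element that cannot be carried out, although the FAS and PP analyses, the adverse-event listing and the laboratory shifts survive. This is a stated analysis that is wrong for the design, and is not detail left to a SAP.

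Second, section XIV does not link PFS to the 4.2 months that sized the trial. The 88 cases agree with a one-sample comparison (86.4 to 88.9 under the three variants shown) and not with a two-group one (309 to 392 events). This rests on exponential PFS, on reading 4.2 and 5.7 months as medians, and on an unstated formula. The hypothesis is still testable with what the Protocol contains; it is left unassembled.

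The randomisation wording in XI.2 and the plural centres in XIII.2 and XV appear to be the same carry-over. They do not affect PFS.

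**What to change.** 1. **Primary analysis.** State a one-sample log-rank test of PFS in the FAS, two-sided at 5% as in XIV.4, against an exponential with median 4.2 months (hazard ln 2/4.2 = 0.165 per month). Report the Kaplan-Meier median with its 95% CI. Success means rejection in the favourable direction, and the conclusion is worded as a comparison with a historical control.
2. **XIV.6.** Name that comparator.
3. **XIV.7.** Replace the two-group tests by single-arm rates with exact confidence intervals. Keep the FAS and PP analyses, the adverse-event listing and the laboratory shifts.
4. **Carry-over text.** Delete the centre-effect and comparability wording. Replace randomisation in XI.2 by one start point that exists in this design, and bring XIII.2 and XV into line with a single centre.
5. **Optional.** A comparison with 4.9 months may be added as a descriptive sensitivity analysis only. At a true 5.7 months its two-sided power with 88 events is Φ(√88 × ln(5.7/4.9) − 1.960) = Φ(1.42 − 1.96), about 29%, so it should not decide success.

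**Cost.** Wording in the Protocol and SAP, with no new data items. The two-sided log-rank test needs about 87 events for 85% power. The existing 88 evaluable cases therefore suffice only if nearly all have progressed or died by the analysis, and the text should say when the analysis is done.

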**III. Inclusion and exclusion criteria**

**1. Inclusion criteria**

1) Women aged between 18 and 70 years；

2)Histologically confirmed Her-2–negative MBC；

3) Not suitable for local treatment;

4) Pretreated with antracyclene and taxane；

5)Prior capecitabine-containing therapy was permitted if the disease had responded to the drug previously and progressed at least 4 months after drug discontinuation；

6)ECOG performance status of no more than 2；

7) Adequate organ function；

8) Having the following laboratory values; WBC≥4×109/L；Hb≥90 g/L；plt≥100×109/L；

9) Written informed consent should be obtained before study procedure.

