**2. Safety assessment**

Safety will be monitored by assessing physical examination, performance status and laboratory examinations. Adverse events will be recorded based on CTC-AE version 3.0.

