**2. During treatment**

Laboratory assessment, physical examination and ECOG performance status will be assessed at the beginning of every cycle.

Chest CT、abdominal MRI and CEA、CA15-3、CA125 will be done every two cycles.

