**IX Usage method and precaution**

**Xeloda**

Drug administration are allowed to delay for 3 weeks in order to allow the toxicity to recover to baseline levels or grade 0~1. However, the dose of capecitabine should be reduced only in the event of severe toxic effects, including: adverse events ≥2 grade 2, such as diarrhea, persistent nausea/vomiting though given preventive measures, hand-foot syndrome (HFS), or elevated liver enzymes (AST and ALT > 2.5×ULN).

Once the patients decrease the dose of capecitabine, the dose will not be increased in the later cycles. But if the administration is interrupted and causes the treatment absence, the later treatment should continue to follow the schedule as planned, and the dose missing due to interruption of treatment should be made up. In addition, if the rest period extended over the next treatment cycle, capecitabine should be given a full dose of 14 days at restart of treatment and the treatment schedule shall be carried out as planned.

Please refer to appendix 5 for the standard dose according to body surface area and dose reduction of capecitabine.

Administration instructions

- Capecitabine of 1000 mg/m2 is given twice every day, from the first day to the 14th day in the cycle of 3 weeks.
- During administration, the patients should be instructed to swallow tablets with water within 30 minutes after meals (breakfast and dinner)
- Daily dose of capecitabine is determined according to the body surface area (BSA), please refer to appendix 5 for the right dose and the number of pills.

Pseudomonas aeruginosa injection (PA-MSHA)

- Manufacturer: Beijing Wanter Bio-pharmaceutical Co., LTD.;
- Properties: milky white liquid, with particles, without sundry;
- Specification: one-time prefilled syringes, with 1 ml/per syringe;
- Storage: 2~8℃ in the absence of light.
- Usage: subcutaneous injection, first dosage of 0.5 ml, then 1 ml/time, every other day (qod).

Precautions:

1) People with a history of allergy should cautiously use it, especially the crowd with a history of multiple drug allergy, who are not suggest to enter the group.

2) A small amount of precipitation may be seen during storage. The refrigerated liquid should be returned to room temperature and fully shaken before using. No block substance or foreign body should be seen.

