**5. Records and reports**

For the adverse events during the test, onset time, symptoms, degree, duration, treatment measures and outcome, etc., should be recorded in case report form. And their relevance to test drugs should be evaluated, and recorded by the researchers in detail. The researcher should sign and date the report. Severity of adverse events will be classified according to the NCI CTC3.0 version. For each symptom, it should be reported the highest classification of the adverse events since the last follow-up.

Relationship between adverse events and the experimental drugs

|  | Certainly relevant | Very possible to be relevant | May be relevant | Suspect | Impossible to be relevant |
| --- | --- | --- | --- | --- | --- |
| With the reasonable time sequence after medication | + | + | + | + | — |
| Known reaction types | + | + | + | — | — |
| Effect relieved or disappeared after removing the drugs | + | + | ± | ± | — |
| Effects appear again when administrate the drugs again | + | ？ | ？ | ？ | — |
| Cannot explain with the patients’ disease | + | + | — | ± | — |

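### The only laboratory-specific safety summary the protocol names is an ungraded normal-to-abnormal count; taken alone, it cannot show worsening from an abnormal baseline or separate trivial from severe shifts

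*Protocol*

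**What the plan says.** Section XIV.7, item 5 (Security analysis) sets out the safety analysis. It states that "adverse events and adverse reactions of the two groups should be listed, including the number of adverse events", and then adds "cases of laboratory examination indexes turned from normal to abnormal before and after the test". That second element is the only summary specific to laboratory values in the statistical section. It names no grade, has no category for patients abnormal at baseline, and does not say which measurement is the later one. (The two-group wording in this single-arm trial is a separate matter.)

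Other sections bear on it:

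- **Monitoring (V.2):** "Safety will be monitored by assessing physical examination, performance status and laboratory examinations".
- **Grading (V.2 and XI.5):** "Adverse events will be recorded based on CTC-AE version 3.0" and "Severity of adverse events will be classified according to the NCI CTC3.0 version". XI.5 also asks, for each symptom, for the highest grade since the previous follow-up.
- **Schedule (VI.2):** "Laboratory assessment, physical examination and ECOG performance status will be assessed at the beginning of every cycle".
- **Entry (III.1):** haemoglobin is allowed from 90 g/L, and liver and renal function are covered by "Adequate organ function", without limits.
- **Capecitabine (IX, Xeloda):** "Drug administration are allowed to delay for 3 weeks in order to allow the toxicity to recover to baseline levels or grade 0~1". The same paragraph names raised AST and ALT among its example adverse events, with a threshold of 2.5 times the upper limit of normal (ULN).

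**The concern.** Safety is a study objective and a secondary endpoint. In a single-arm trial, laboratory toxicity can be judged only against outside rates, and the rates that the introduction cites (section I.2) are graded. For example, grade 3 or 4 leukopenia is given as 11% with capecitabine alone and 68% with its combination partner. An ungraded count of values leaving the normal range is a different quantity and cannot be compared with those figures.

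The count also has a blind spot where the entry criteria leave room for abnormal values. A patient who starts outside the normal range cannot turn from normal to abnormal, however far the value worsens. The protocol calls for CTC 3.0 grading and a laboratory assessment every cycle, but the one laboratory summary it names asks for neither.

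**Working it through.** The plan gives no figure to reproduce here. The check sets the wording of XIV.7, item 5 beside the grading, schedule and entry text and follows three hypothetical kinds of patient.

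**1. Three patient types**

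- **A: abnormal at entry, then worse.** Examples are haemoglobin from 92 to 64 g/L, or ALT from 1.5 to 8 times ULN. The haemoglobin example assumes that the lower limit of normal lies above 92 g/L; the protocol gives no reference range.
- **B: normal at entry, toxic during treatment, normal at the end.** An example is an AST rise above 2.5 times ULN that resolves during a delay of capecitabine.
- **C: normal at entry, abnormal later.** One patient is just outside the limit and another is at grade 4.

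**2. How each is scored**

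| Patient | Count, if the later value is the last one | Count, if it is any on-treatment value | Baseline grade by worst grade |
| --- | --- | --- | --- |
| A | not counted | not counted | shown, if the grade worsens |
| B | not counted | counted, no grade | shown at worst grade |
| C, trivial | one case | one case | shown at its grade |
| C, grade 4 | one case | one case | shown as grade 4 |

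Failure A holds under either reading, and so does the equal weighting in C. Failure B depends on the reading, which item 5 leaves open. The per-cycle schedule in VI.2 makes the any-value reading possible but does not establish it.

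**3. The adverse event route**

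XI.2 sends all adverse events in the reporting period, related or not, to the case report form. V.2 and XI.5 grade them by CTC 3.0, and XI.5 keeps the highest grade since the last follow-up. IX treats raised liver enzymes as an example of an adverse event. Patients A and B can therefore be recorded there, with a grade that recovery does not erase.

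Two gaps remain:

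- Section XI gives no rule for when an out-of-range laboratory value becomes an adverse event, and its highest-grade rule is worded by symptom.
- XIV.7, item 5 asks for the number of adverse events. It does not ask for them by grade, so a grade that is collected need not reach the stated analysis.

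**4. How many patients fall outside the count**

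If a share p of the 96 patients is abnormal at entry on a given test, 96 × p of them cannot contribute to the count for that test. The documents give no value for p. As an assumed range:

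- p = 20%: 96 × 0.20 = 19.2, about 19 patients.
- p = 40%: 96 × 0.40 = 38.4, about 38 patients.

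This is the number the summary cannot register, not the number of toxicities lost to the trial. Entry also requires WBC of at least 4×10⁹/L. If that is at or above the local lower limit (an assumption), the baseline problem concerns haemoglobin and chemistry more than leukopenia.

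**The case against.** The strongest reply is that the count does not stand alone. It is one item in a list introduced as inclusive, next to the number of adverse events. Every adverse event is recorded and graded, and the highest grade is kept. An enzyme rise that led to a dose reduction is an adverse event in the protocol's own terms, even if it was normal again by the end. This stands. A reader might infer that laboratory toxicity is counted only through this shift, or that severe and recovered toxicity goes uncounted in the trial. The documents do not support either inference.

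A second reply is that no bias is shown. This also stands. Leaving out patients abnormal at entry lowers the count, while scoring trivial shifts raises it, so the net direction is undetermined. A reader might take 10% as the rate of grade 3–4 worsening, so that 9.6 of 96 patients are severe cases, and conclude that about 2 to 4 of them are missed (9.6 × 0.20 = 1.9; 9.6 × 0.40 = 3.8). Both the rate and the baseline shares are assumptions, and the step ignores the adverse event route.

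A third reply is that shift tables belong in the statistical analysis plan, which is not shown and may contain them. This stands in part. Because the list in item 5 is not exhaustive, such a plan could add graded tables without contradicting the protocol. But the point is not that detail is absent. The protocol itself names a laboratory measure, and the measure it names is a poor one.

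**Conclusion.** The point holds as a weakness in the named laboratory summary and is worth correcting. Two defects follow from the wording under any reading: blindness to worsening from an abnormal baseline, and no distinction by severity. The loss of recovered toxicity is conditional on the later value being the final one. The adverse event route reduces the harm but does not repair the measure, because it rests on an unstated rule for laboratory values and on a count without grades.

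The practical consequence is that the stated analysis yields no graded laboratory rate to set beside the cited capecitabine data. No claim is made on the net direction or size of bias. The conclusion rests on one assumption: that some patients enter with an abnormal value, which the entry criteria appear to allow but which no figure in the documents confirms.

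**What to change.** In section XIV.7, item 5, replace the normal-to-abnormal count with a table of baseline CTC 3.0 grade by worst on-treatment CTC 3.0 grade for each laboratory test, in the safety set. Use all per-cycle values from VI.2 and any unscheduled values. For each test, report the number and percentage of patients with worsening of one grade or more, and the number and percentage with worst grade 3–4. This removes the need to interpret which value is the later one, and it does not depend on whether an investigator recorded the value as an adverse event.

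The cost is a change of analysis wording and slightly more tabulation. The assessments are already scheduled every cycle, so no new scheduled tests are needed. If the statistical analysis plan already contains such a table, aligning item 5 with it is enough.
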